### Interventions

#### ACPG group

Patients in the ACPG group will be treated IV with 18–24 million units of ACPG per day, consisting of 3–4 million units every 4 h, for 14 days, followed by intramuscular injections of benzathine penicillin, 2.4 million U per week, for 3 weeks, in accordance with Chinese, American, and European guidelines [5, 6, 16].

#### Ceftriaxone group

Patients in the ceftriaxone group will be treated IV with 2 g ceftriaxone per day for 10–14 days, followed by intramuscular injections of benzathine penicillin, 2.4 million U per week, for 3 weeks, in accordance with previous guidelines [6, 16].

Prior to treatment with ACPG or ceftriaxone, patients will be treated with glucocorticoids to prevent the occurrence of adverse reactions, such as Jarisch–Herxheimer reaction (JHR), as determined by clinicians. Patients with worsening mental disorders or severe adverse events due to treatment were allowed to discontinue treatment. After treatment, patients will be followed up every 3 months for the first year, with clinicians informing patients of return visits by telephone.

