##### Adverse events

The JHR is the most common transient clinical phenomenon that occurs in patients infected by syphilis who undergo antibiotic treatment. JHR can manifest as fever, chills, rigor, nausea and vomiting, headache, tachycardia, hypotension, hyperventilation, flushing, myalgia, and exacerbation of skin lesions. Although occurring very rarely in patients with late syphilis, the JHR can occur in 75% of patients with general paresis [22]. The present study will compare JHR rates in the ACPG and ceftriaxone groups. Other adverse events due to treatment, such as neurotoxicity and neutropenia, will also be analyzed [23]. All adverse events after treatment and at each follow-up visit will be recorded.

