### Blinding

Because of the obvious differences between modes of administration of ACPG and ceftriaxone, both patients and clinicians will be aware of their group assignment, precluding the possibility of a double-blind study design. However, the outcome assessors and data analysts can be masked (blinded) to the treatment assignment. This prospective randomized open-blinded endpoint (PROBE) study design is frequently used to improve the reliability of analytic results [26].

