### Statistical analysis

All statistical analyses will be performed using SPSS 21.0 statistical software by biostatisticians blinded to group assignment. Missing data for the primary outcome will be imputed using the multiple imputation method. Serum and CSF RPR titers will be analyzed after log_2_ conversion. Normally distributed continuous variables in the two groups will be compared by *t* tests, and categorical variables will be compared by the *χ*^2^ test or *Fisher’s *exact test, as appropriate. Nonparametric variables will be compared by rank sum tests. The correlation between serum and CSF RPR titers will be analyzed using Spearman’s rank correlation tests. Based on the assumption that there are no obvious correlations between primary outcomes and that it will be impossible to determine which outcome has greater weight, the weights of these primary outcomes will be evaluated using the “Experts Scores” algorithm, with “overall response” to treatment evaluated according to the total efficacy scores from these primary outcomes. The results of each primary outcome will also be evaluated separately. The non-inferiority margin will be set at 10 percentage points for the absolute difference between the two groups. If the standard for non-inferiority is reached, all primary and secondary outcomes will be tested for superiority (*P*<0.05). Non-inferiority will be considered reached if conclusions drawn from the intention-to-treat (ITT) population, consisting of all patients who met the inclusion criteria, were randomized, and started treatment, and the per-protocol population, consisting of all patients with good compliance and who followed the protocol to completion of the treatment regimen, are consistent. Univariate analyses will be performed to identify potential factors associated with the treatment outcome, with variables having a *P* value ≤0.10 in univariate analyses included in a multivariate logistic regression model. Odds ratios (ORs), adjusted ORs (aORs), and their 95% confidence intervals (CIs) will be calculated. A two-sided *P value* <0.05 will be considered statistically significant. Because the efficacy and safety of ceftriaxone and ACPG are clear and both are recommended by Chinese National Guidelines, this trial will not include interim analyses.

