This trial will meet high methodological standards, such as strict inclusion and exclusion criteria, adequate randomization and concealment of allocation, a PROBE design, the inclusion of independent statisticians, and multilevel quality control. These factors increase the credibility of the clinical trial results. Second, comprehensive outcomes will be evaluated to compare the efficacy of ACPG and ceftriaxone. Previous clinical trials have evaluated the efficacy of treatment for neurosyphilis based on rates of serological cure, clinical cure, and normalization of CSF-WBC counts and on protein concentrations [17, 27–30]. Several studies have also evaluated the use of neuroimaging examinations to determine the efficacy of neurosyphilis treatments [21, 31]. The present trial will also evaluate clinical improvements (including MMSE scores), adverse events, time to recovery, and recurrence of neurosyphilis. Evaluation of improvements in clinical manifestations will include improvements of the most common clinical manifestations of each clinical subtype of neurosyphilis during follow-up. These parameters have not yet been evaluated in previous studies and may provide strong evidence to determine the efficacy of treatment. Adverse events will be assessed to determine the safety of ceftriaxone. Disease recurrence, time to recovery, and 1-year follow-up results in patients with neurosyphilis may provide evidence for evaluating the long-term efficacy of the two drugs. In addition, because neurosyphilis patients are frequently lost to follow-up, the sample size calculated using a standardized formula has been increased to improve the reliability of outcomes. Finally, analysis of clinical factors, such as smoking, alcoholism, stage of disease (early or late neurosyphilis), asymptomatic or symptomatic status, baseline serum and CSF RPR titer [32], and CSF-WBC counts and protein concentration, may enable the identification of the factors related to treatment efficacy and obtain evidence for providing a more personalized and accurate treatment regimen.

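### Glucocorticoid prophylaxis against JHR is left to clinicians who know the allocation, with no stated timing, so the between-arm JHR comparison is open to unequal co-treatment

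*Protocol article*

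**What the plan says.** All of this is in the protocol article.

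- **Interventions, Ceftriaxone group.** Before ACPG or ceftriaxone, "patients will be treated with glucocorticoids to prevent the occurrence of adverse reactions, such as Jarisch–Herxheimer reaction (JHR), as determined by clinicians". The sentence covers both arms. It gives no criteria for use, and does not place the decision before or after randomisation.
- **Blinding.** The trial is open label for those who prescribe: "both patients and clinicians will be aware of their group assignment, precluding the possibility of a double-blind study design". Masking is foreseen elsewhere: "the outcome assessors and data analysts can be masked (blinded) to the treatment assignment".
- **Adverse events** (listed under Secondary outcomes). "The present study will compare JHR rates in the ACPG and ceftriaxone groups". The same paragraph calls JHR very rare in late syphilis but says that "the JHR can occur in 75% of patients with general paresis".
- **Statistical analysis.** Categorical variables are compared by the chi-square or Fisher's exact test. No allowance for steroid use is described.
- **Discussion.** The examples of factors to be analysed ("analysis of clinical factors, such as smoking, alcoholism, stage of disease (early or late neurosyphilis), asymptomatic or symptomatic status", then baseline RPR titer, CSF-WBC count and protein) do not include steroid use.

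**The concern.** A drug given specifically to prevent JHR is prescribed at the discretion of people who know the arm, and JHR is then compared between the arms. If clinicians give steroids more often, at a different dose or at a different time in one arm, the observed JHR rates mix the effect of the antibiotic with the effect of the prescribing. A difference could appear where there is none, or a real one could be masked.

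Masked assessment does not help, because the bias would enter through the co-treatment and not through measurement. Randomisation protects the comparison only as far as the steroid decision cannot respond to the allocation. Adjusting afterwards for steroids actually given would not fully repair it, since a choice made after allocation is confounded by indication.

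At stake is part of the safety comparison. The Discussion says that adverse events will be used to judge the safety of ceftriaxone.

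**Working it through.** The article gives no figure for steroid use or for JHR in the trial population, so there is no stated result to reproduce. What follows illustrates possible size only.

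**Inputs from the article:** 290 patients randomised 1:1, so 290 / 2 = 145 per arm; two-sided 0.05; JHR of 75% in general paresis only.

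**Assumptions, not in the article:** the same untreated JHR rate p in both arms (10%, 30% or 75%); steroid risk ratio RR for JHR between 0.3 and 0.8; steroid use u of 70% in one arm and 30% in the other.

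**1. Creating a difference.** The expected JHR rate in an arm is p × [1 − u × (1 − RR)]. The spurious gap is therefore p × (1 − RR) × (u₁ − u₂), here with u₁ − u₂ = 0.40.

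| Untreated rate p | RR 0.8: arm rates, gap | RR 0.3: arm rates, gap | Chance of P<0.05 across this range |
|---|---|---|---|
| 10% | 8.6% vs 9.4%, 0.8 points | 5.1% vs 7.9%, 2.8 points | about 4% to 16% |
| 30% | 25.8% vs 28.2%, 2.4 points | 15.3% vs 23.7%, 8.4 points | about 7% to 44% |
| 75% | 64.5% vs 70.5%, 6.0 points | 38.25% vs 59.25%, 21.0 points | about 19% to 95% |

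For example, 0.30 × (1 − 0.3) × 0.40 = 0.084. The last column counts significance in the direction of the gap only, where 2.5% is expected by chance. With equal use in both arms the gap is 0 in every row.

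**2. Hiding a difference.** Take true untreated rates of 30% and 20% and RR 0.5.

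- Use of 50% in both arms: 0.30 × (1 − 0.5 × 0.5) = 22.5% and 0.20 × (1 − 0.5 × 0.5) = 15.0%. The difference is visible.
- Use of 80% and 20%: 0.30 × (1 − 0.8 × 0.5) = 18% and 0.20 × (1 − 0.2 × 0.5) = 18%. The difference has gone.

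**3. If every patient receives steroids.** Then u = 1 in both arms and the gap above is zero. A gap can still arise if dose or timing makes the steroid effect differ by arm; it is then p × (RR₁ − RR₂).

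**The case against.** Several points on the other side stand, and they limit how far this can be taken.

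- **Timing.** A reader might infer that the steroid choice is made with the allocation in view. The article says only that steroids come before the study drug. A decision after allocation is plausible in an open-label trial, but it is not stated.
- **Who gets steroids.** The start of the sentence can be read as covering every patient, with only the details left to clinicians. On that reading, use cannot differ by arm; only dose or timing can.
- **Motive.** The article ties JHR to disease type, not to the antibiotic. If clinicians choose by disease features alone, randomisation balances that choice in expectation. Unequal use is a risk, not a reported fact.
- **Sites.** A reader might infer that different practice at the five centres biases the comparison. With 1:1 blocked allocation and 58 patients per centre, site variation alone does not.
- **Size.** Applying 75% to whole arms, with use of 80% versus 40% and RR 0.5, gives 0.75 × 0.5 × 0.40 = 15 points. The 75% belongs to general paresis, one of five named subtypes. The article does call it the most frequently reported presentation in China, but gives no JHR rate for the trial population.
- **Detail held elsewhere.** Treatment information is recorded at each visit, and SOPs for interventions exist. Steroid criteria may well be in documents not shown.

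The last point does not dispose of the matter. Recording use does not keep it equal, and nothing shown says that the SOPs fix the steroid decision independently of the arm. The article does state a rule, clinician discretion, and that rule is poorly fixed for the comparison it announces. An analysis plan could not fully repair this later.

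**Conclusion.** The point holds as a risk to one secondary safety outcome. Discretionary prophylaxis aimed at JHR, clinicians who know the arm and a planned between-arm JHR comparison are all in the text, and nothing shown keeps steroid use, dose or timing alike in the two arms.

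The size cannot be known from the article. Under the assumed 70% versus 30% use and RR of 0.3 to 0.8, it runs from under 1 point at an untreated rate of 10% to 21 points at 75%. The upper figures apply only if the general paresis rate held for the whole trial, which the article does not claim.

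A reader might also infer that the primary non-inferiority conclusion is compromised. The documents do not support that: JHR is not a primary outcome, and the article states no link between steroid use and the primary outcomes. The change is worth making because it is cheap and closes a route of bias that later analysis cannot fully remove.

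**What to change.** 1. Reconcile the two halves of the glucocorticoid sentence, so that it is clear whether all patients are treated or clinicians select them, and when the decision is made. Whether and how steroids are given stays with the sponsor.
2. For patients still to be randomised, have the steroid decision made and recorded on the CRF before the allocation is opened. Record any later change as a deviation.
3. Report actual steroid use by arm for all patients.
4. Show JHR by arm within strata of the pre-allocation decision where it is available. This stratifier is safe because the allocation cannot influence it. Describe the JHR comparison for earlier patients as open to unequal co-treatment.

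**Cost.** One sentence, one CRF field, some deviation records and two tables; no extra patients. Recruitment began on 1 December 2021, so the stratified table will not cover patients already randomised.

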### Outcomes

All parameters will be assessed at baseline before treatment (T0) and at follow-up timepoints 3 (T1), 6 (T2), 9 (T3), and 12 (T4) months later.

#### Primary outcomes

##### CSF white blood cell (WBC) count

CSF-WBC count is a sensitive indicator of the curative effect of interventions on neurosyphilis, with Chinese National Guidelines recommending that CSF-WBC count be assessed at 6-month intervals. In this trial, a significant reduction in CSF-WBC count or return to a normal range (<5×10^6^/L in the absence or ≤ 20×10^6^/L in the presence of HIV coinfection) after treatment was defined as effective.

##### CSF syphilitic serological response

In this study, serological cure was defined as a CSF RPR titer that decreased by two dilutions or showed reversion to nonreactivity within 1 year after treatment. CSF RPR titers will be measured at 6 and 12 months after treatment.

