##### Serum syphilitic serological response

In this study, clinical cure was defined as a serum RPR titer that decreased by two dilutions or showed reversion to nonreactivity within 1 year after treatment. Serum RPR titers will be measured every 3 months for 1 year after treatment.

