##### Improvement of clinical manifestations

Improvements in clinical manifestations are essential in evaluating the efficacy. These improvements will be evaluated among patients with different clinical subtypes of neurosyphilis, such as meningitis syphilis, meningovascular syphilis, general paresis, tabes dorsalis, and ocular syphilis. The presence of the main clinical symptoms of each subtype (Table 2) will be assessed at baseline. Outcomes evaluated during follow-up treatment will include whether each symptom worsened, persisted (no change), recurred (initially improved, but later worsened with no further improvement), improved (clinically relevant improvement without a return to baseline), or recovered (total disappearance of symptoms).

**Table 2 Tab2:** Clinical manifestations among different subtypes of neurosyphilis

Subtype	Clinical manifestations
**Meningitis syphilis**	Fever
	Headache
	Nausea and vomiting
	Stiff neck
	Meningeal irritation
	Diminution of vision
	Diplopia
	Ptosis
	Facial paralysis
	Hearing loss
	Lower limb weakness
	Paresis, paraplegia
	Gatism
**Meningovascular syphilis**	Hemiplegia
	Aphasia
	Epileptic seizure
	Diffuse pain at the innervation site of the affected nerve
	Defecation disorder
	Hypomyotonia, amyotrophy
**General paresis**	Attention-deficit disorder
	Forgetfulness, poor judgment, and memory
	Cognitive disorder
	Dementia
	Depression
	Personality changes
	Delusion
	Mania
	Amentia
	Epileptic seizure
	Stroke
	Dysarthria
	Hypotonia in the face and limbs
	Involuntary movements of the face, tongue, and hands
**Tabes dorsalis**	Sensory ataxia
	Lightning pain in the lower limbs
	Uroschesis
	Visceral crises
	Lower extremity muscle tone is low
	Charcot joint
	Optic atrophy
	Argyll Robertson pupil
	Tendon reflexes decreased or absent
**Ocular syphilis**	Blepharoptosis
	Limitation of eye movement
	Diplopia
	Diminution of vision
	Blind
	Bulbar conjunctival hyperemia
	Visual field defect
	Metamorphopsia
	Color vision
	Dimmed vision
	Aethomma, floaters

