##### Nonresponse to treatment

Nonresponse will be defined as persistent symptoms, a sustained titer of CSF-VDRL/RPR (i.e., the titer did not decrease by two dilutions or showed reversion to nonreactivity), or an elevated CSF-WBC count during the 12-month follow-up.

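### The primary efficacy definitions set no condition on further anti-treponemal therapy, so a cure obtained after retreatment is credited to the assigned drug and favours non-inferiority

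*Protocol article*

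**What the plan says.** All references are to the protocol article.

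- *CSF syphilitic serological response*: "serological cure was defined as a CSF RPR titer that decreased by two dilutions or showed reversion to nonreactivity within 1 year after treatment". On timing: "CSF RPR titers will be measured at 6 and 12 months after treatment".
- *Serum syphilitic serological response*: "clinical cure was defined as a serum RPR titer that decreased by two dilutions or showed reversion to nonreactivity within 1 year after treatment", with serum titres read every 3 months.
- *CSF white blood cell (WBC) count*: a significant reduction, or a return to the normal range, after treatment is effective.
- *Nonresponse to treatment*, a secondary outcome: "Nonresponse will be defined as persistent symptoms, a sustained titer of CSF-VDRL/RPR", or an elevated CSF white cell count during the 12 months. Retreatment is not mentioned, and nothing makes this outcome override a primary-outcome cure.
- *Statistical analysis*: the ITT set is defined as "consisting of all patients who met the inclusion criteria, were randomized, and started treatment". The per-protocol set is defined as "consisting of all patients with good compliance and who followed the protocol to completion of the treatment regimen". Non-inferiority needs consistent conclusions from both sets, against a margin of 10 percentage points on the absolute difference.
- *Interventions*: each arm's regimen ends with weekly benzathine penicillin for 3 weeks. The article says nothing about retreatment, rescue or additional antibiotics after that.

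**The concern.** The trial asks whether ceftriaxone is no worse than ACPG. A titre that falls because of a second course says nothing about the first, yet the definitions look only at whether the response occurred and not at what produced it. With CSF read at months 6 and 12, a patient who has not responded at month 6 can receive further therapy and be a cure at month 12.

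The direction is predictable. The arm with more first-course failures has more patients to convert, so conversion narrows any true difference. In a superiority trial that would be conservative; here it favours the claim. The usual safeguard, agreement between ITT and per-protocol, does not help if both sets contain the same converted patients. Multiple imputation does not help either, because these patients' outcomes are observed, not missing. The stated aim is evidence for wider use of ceftriaxone and for guideline change, so a false positive would matter.

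**Working it through.** **How the definitions classify the patient.** Take a patient who completes the assigned course, has no two-dilution fall in CSF RPR at month 6, receives further anti-treponemal therapy, and is nonreactive at month 12.

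- CSF definition: reversion within 1 year, so a cure. The serum and white cell definitions work the same way, and the total efficacy score behind overall response inherits the result.
- ITT: eligible, randomized and started treatment, so included as a cure.
- Per-protocol: the condition runs to completion of the treatment regimen, which this patient met before retreatment. Exclusion criteria 5 and 6 in Table 1 concern adherence to the regimen, follow-up, termination and withdrawal, not later therapy. The most natural reading is included as a cure.

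**The plan's own figures.** Events: 7.85 × (1 + 1.5)² / (1 − 1.5)² = 7.85 × 25 = 196.25, against 196 stated. Participants: 196 / 0.85 = 230.6, against 230. Recruitment: 230 / (1 − 0.20) = 287.5, so 288, against 290 (58 × 5). These reproduce and do not depend on this point. They supply the inputs below.

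**Inputs.**
- From the article: n = 230 / 2 = 115 per arm (or 290 / 2 = 145 if everyone recruited is counted); margin 10 points; ACPG success rate 85%, the expected rate used for the sample size.
- Assumed: ceftriaxone first-course success 75%, exactly at the margin; non-inferiority judged from a two-sided 95% interval (one-sided 2.5%); one binary outcome; the same fraction q of first-course failures converted to counted cures in each arm.

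**Formulas.** Counted rates: p_A = 0.85 + 0.15q and p_C = 0.75 + 0.25q, so the counted difference is 0.10 × (1 − q). Standard error: SE = √[(p_A(1 − p_A) + p_C(1 − p_C)) / n]. Probability of declaring non-inferiority ≈ Φ((0.10 − (p_A − p_C)) / SE − 1.96).

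Example, q = 0.4, n = 115: p_A = 0.91, p_C = 0.85, SE = √[(0.0819 + 0.1275) / 115] = 0.0427. Then 0.04 / 0.0427 − 1.96 ≈ −1.02, which gives 0.153.

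| q | Counted rates | Difference | n = 115, approx. | n = 115, exact binomial | n = 145, exact binomial |
|---|---|---|---|---|---|
| 0 | 85% vs 75% | 10 | 2.5% | 2.7% | 2.6% |
| 0.1 | 86.5% vs 77.5% | 9 | 3.9% | 4.3% | 4.3% |
| 0.2 | 88% vs 80% | 8 | 6.1% | 6.7% | 7.2% |
| 0.3 | 89.5% vs 82.5% | 7 | 9.7% | 10.5% | 11.9% |
| 0.4 | 91% vs 85% | 6 | 15.3% | 16.5% | 19.5% |

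The exact columns sum the binomial probabilities of every outcome pair whose Wald 95% interval excludes a 10-point deficit. The q = 0 row is also the result if every converted patient is scored as a nonresponder.

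**The case against.** **Silence, not error.** The article never mentions retreatment, and an analysis plan or the operating procedures for result evaluation (*Quality control*) may carry a handling rule. That is fair as to what may exist elsewhere. But the cure definitions are in the article, and as worded they already give an answer for a retreated responder. The point concerns that answer, not a missing detail.

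**The per-protocol set may exclude these patients.** Good compliance and following the protocol could be read that way. This stands as a possibility, so the per-protocol half of the point is a reading and not a certainty. The ITT half does not depend on it.

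**Counting outcomes regardless of later therapy is a recognised strategy.** It is, but for non-inferiority it is anti-conservative, so it suits a sensitivity analysis better than the primary one. Conversely, scoring retreated patients as nonresponders makes the outcome depend partly on unblinded clinicians' decisions, and some month-6 nonresponders might have responded by month 12 without retreatment. Both drawbacks are real.

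**Stronger readings that the article does not support.**
- A reader might infer that clinicians can retreat poor responders with the other arm's drug. No section says so.
- A reader might infer from the symptom category "recurred (initially improved, but later worsened with no further improvement" that a relapse rescued by retreatment is never a recurrence. That wording governs the symptom grading only. *Recurrence of neurosyphilis* has no such condition and counts recurrent symptoms, or a CSF result that reverts. It is a secondary outcome, though, and does not undo a primary cure.
- A reader might infer that outcomes are judged by people who know the allocation. *Blinding* says that outcome assessors and data analysts can be masked. Masking would not remove this problem, since a masked reader would correctly record a fall caused by a second course.

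**Conclusion.** The point holds as a defect in how the primary outcomes are scored. Response is credited whatever produced it, so a cure after further therapy counts for the assigned drug in ITT and, on the most natural reading, in per-protocol. The bias is toward non-inferiority: the counted difference is (1 − q) times the true one.

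Its size cannot be fixed from the article, which gives no retreatment rate. At 85% versus 75% with 115 per arm, false non-inferiority goes from about 2.5% to about 4% at 10% conversion, 6–7% at 20% and 15–17% at 40%. This rests on equal conversion in both arms, a single binary outcome and a true difference exactly at the margin; the weighted overall response could behave differently. If few patients are retreated, the effect is small. The rule should still be settled before anyone sees results by arm, because one chosen afterwards would be open to challenge.

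**What to change.** Add to the primary outcomes and the statistical analysis section:

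1. In the primary non-inferiority analysis, a patient who receives further anti-treponemal therapy for persistent or recurrent neurosyphilis before month 12 is a nonresponder to the assigned drug on each primary outcome and on overall response. Further therapy means therapy beyond the complete assigned regimen, including its benzathine penicillin injections.
2. Assessors masked to allocation confirm from the recorded treatment data that the reason was persistent or recurrent disease. *Management of data and biological samples* already provides for diagnosis and treatment information at each visit.
3. State that the rule applies in both the ITT and the per-protocol set.
4. Report as sensitivity analyses the as-observed (treatment-policy) result and the effect of anti-treponemal antibiotics given for other indications.

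The cost is definition wording, a case report form flag, a masked check of the flagged patients and the added analyses, with no extra visits or patients. Counted response rates fall slightly, and the primary outcome depends in part on open-label treatment decisions; the as-observed analysis shows how far that matters. The change concerns outcome scoring only, not whether, when or how anyone is retreated.
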